##### Caregiver and Hub practitioner interviews

Twelve months after Hub implementation begins, we will conduct realist-informed semi-structured interviews with 18–24 caregivers and 5–10 Hub practitioners per site.^64^ We will purposively sample participants to capture caregivers from diverse cultural backgrounds, experiences of adversities and varying levels of engagement with intersectoral services. These realist-informed interviews will enhance the testing of the initial programme theory to triangulate with the findings from the quantitative measures. The interviews aim to uncover (i) the mechanisms and contextual elements relevant to the Hub models (to inform theory development), (ii) acceptability and feasibility of the Hub, (iii) their experience of being asked about adversity, the care offered to them and the process of referrals including barriers and enablers to uptake (caregivers only) and (iv) confidence and competence in detecting and supporting families experiencing adversity (practitioners only).

#### Quantitative data analysis

Statistical analyses will be conducted using Stata or R statistical software packages.^65 66^ The baseline characteristics of the caregivers, children and practitioners will be described using the mean, median and IQR for continuous data and proportions for categorical data. Primary and secondary outcomes will be assessed by examining change in proportions/means from baseline to 6 months, from 6 to 12 months and from baseline to 12 months. We will also conduct linear regression analyses to assess the association between each caregiver-reported primary outcome at 6 and 12 months with the outcomes of child and caregiver mental health and caregiver quality of life, at 6 and 12 months, respectively.

Quantitative measures of the strength and structure of service linkages between Hub practitioners will be analysed using social network analysis (SNA) software package UCINET.^67^ SNA is a complex systems discipline and quantitative methodology widely used to measure networked relationships between organisations and individual actors in health service and policy settings.^68–71^ UCINET^67^ will calculate indicators (ie, density, degree, centrality and betweenness) for the network and each Hub practitioner based on: (i) contact, (ii) referrals to and from and (iii) quality of the relationship. These indicators and analytical approach are recommended for descriptive social network analysis.^68–71^

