## Introduction

### Family adversity and its negative impact on mental health

Interventions aimed at reducing or preventing the impact of adversity on children could avert a substantial proportion of the population burden of mental illness, and build on evidence demonstrating the health and economic benefits of investing early in life.^1^ Family adversity includes a range of adverse childhood experiences (ACEs) such as childhood maltreatment (eg, physical, verbal or sexual abuse), household dysfunction (eg, parental mental illness, family substance abuse), community dysfunction (eg, witnessing physical violence, discrimination), peer dysfunction (eg, stealing, bullying) and socio-economic deprivation.^2^ While family adversity can negatively impact a range of physical and mental health outcomes, its negative effects on children’s mental health are well established, increasing the risk of anxiety, depression and suicidality in childhood and across the life course.^3–8^ Further, exposure to multiple ACEs predicts greater odds of poorer mental versus physical health outcomes in adult life.^9^ Experiences of family adversity also negatively affect child’s neurological and physiological development and educational outcomes,^10^ which in turn lead to poor life-long health and mental health outcomes.^11^

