### Study phase 1: development of initial Hub programme theory through formative research

The initial Hub programme theory was developed through an intensive formative research phase during which we collected contextual information and co-designed the Hub models with intersectoral (eg, health, social, legal and education) practitioners and caregivers from each local community. This phase occurred from October 2020 to June 2021 in Victoria and January to August 2021 in NSW. First, a historical and current needs assessment of the health, social, legal and community contexts of each site was conducted using qualitative data from online group discussions, individual interviews and meetings with key stakeholders including intersectoral practitioners (ie, from health, social, legal and community sectors) and caregivers. We used CFIR^42^ to capture and synthesise these data into barriers and enablers across the outer setting, inner setting, individual level, process and intervention components.

Second, we reviewed the HHAN programme theories and other relevant realist literature focused on integrated care for children and families experiencing adversity^23 30 56–59^ to identify key CIMO configurations relevant to the Hubs. HHAN provided a useful starting point because our study builds on the HHAN model of care. For pragmatic reasons, we focus the process and outcome evaluation in this study on three key mechanisms and associated CIMO configurations in the initial programme theory. Namely, (1) trust between caregivers and the service/practitioners, and between practitioners, (2) knowledge acquisition and motivation of practitioners and (3) perceived benefits of collaboration by practitioners. Figure 2 displays the initial realist-informed programme theory. We then formulated the logic model displayed in figure 3 proposing how the Hub models will be investigated and are theorised to contribute to outcomes. The logic model includes how immediate outcomes, that is, increased detection and response to adversity are hypothesised to lead to our intended outcomes, including increased uptake of services and improved child and caregiver mental health and caregiver quality of life.

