### Study phase 2: testing of initial Hub theory using empirical data

We will empirically test the initial programme theory for the Hubs through a mixed-methods process with 6 and 12 months outcomes evaluation. The evaluation aims to assess for whom, how and why the Hub models had an impact (if any) in the two different contexts of Wyndham Vale and Marrickville across the child, caregiver, practitioner and system level outcomes specified in figures 2 and 3, table 1 and ‘Outcomes Assessment’ below.

**Table 1 T1:** Primary and secondary outcomes

Primary outcomes		Baseline assessment		6 and 12 months post Hub implementation begins	
		**Caregiver survey**	**Practitioner survey**	**Caregiver survey**	**Practitioner survey**
*Caregiver*					
Identification of adversity	Increase in the proportion of caregivers who report being asked by a service provider about adversity in the past 6 months.	X		X	
Intervention for adversity	Increase in the proportion of caregivers who report spending extra time with or receiving an intervention from a Hub service provider for adversity in the past 6 months.	X		X	
Referrals for adversity	Increase in the proportion of caregivers who report receiving a referral to an intersectoral service for adversity in the past 6 months.	X		X	

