##### Caregivers

Potential caregiver participants are those who: (i) care for a child aged 0–8 years, including women who are pregnant, (ii) access any of the universal or specialist services provided in the Hub, such as general practitioners (GPs), paediatricians, lawyers and (iii) can understand written or spoken English language. The English language criterion is a limitation of our study; however, funding is not available to provide interpreters. Furthermore, culturally and linguistically diverse persons participated in an informed and meaningful way in phone-based or in-person surveys for HHAN (personal communication [name]).

Given the preventative focus of this study, caregivers will not be screened for adverse experiences as an inclusion criterion. Instead, caregivers will report the frequency of 15 adversity types in the baseline survey. These adversity types are derived from the Parent Engagement Resource^61^ and include challenges with: social support, finances, housing, employment, family physical health, parent mental health, parenting, child neglect, alcohol and substance use, family relationships, family violence, child abuse, visa and immigration issues, crime issues and discrimination.

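### The regressions of mental health and quality of life on the primary outcomes pair measures from the same survey wave and name no adjustment, so as written they cannot separate response from the need that prompted it

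*Protocol article*

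**What the plan says.** The Quantitative data analysis section of the protocol article announces linear regressions "to assess the association between each caregiver-reported primary outcome at 6 and 12 months with the outcomes of child and caregiver mental health" and with "caregiver quality of life, at 6 and 12 months, respectively". The last word fixes the pairing: exposure and outcome come from the same survey. No covariate is named.

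In Table 1 the exposures are recalled over the preceding six months. Identification is defined as "Increase in the proportion of caregivers who report being asked by a service provider about adversity in the past 6 months", and referral as "Increase in the proportion of caregivers who report receiving a referral to an intersectoral service for adversity in the past 6 months". Intervention is defined in the same way.

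The Caregivers section says that "caregivers will not be screened for adverse experiences as an inclusion criterion". Adversity is nonetheless recorded at entry, since the same section adds that "caregivers will report the frequency of 15 adversity types in the baseline survey". On the effect of family adversity, the Introduction says that "its negative effects on children’s mental health are well established". Under Study phase 1, the logic model runs the other way for the response: "increased detection and response to adversity are hypothesised to lead to our intended outcomes", which include better child and caregiver mental health and caregiver quality of life.

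**The concern.** In these regressions the primary outcomes act as exposures. A referral or intervention for adversity goes to families who have adversity. With no selection on adversity, the comparison group includes families with nothing to treat or refer. The protocol itself holds that adversity worsens children's mental health, so the helped group would be expected to start from a worse position. That difference works against the direction the logic model predicts.

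The Health economics analysis section sharpens the point. It uses the child questionnaires to determine perceived need, whereas the regression treats the same domain as a result of the response. Measured once, in the same wave as the exposure, a score cannot be assigned to one role or the other.

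At stake is the step from detection and response to better outcomes. The other planned caregiver analysis examines change in proportions and means over time and does not link the two. The limitation stated at the front of the article concerns the missing comparison group, not confounding within this regression.

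**Working it through.** **Figure in the plan.** The only number bearing on the regression is the caregiver total. Two sites at 100–200 each give 2 × 100 = 200 to 2 × 200 = 400, which matches the Sample size calculation section. The article gives no event rates, standard deviations, correlations or effect sizes, so every other input below is an assumption.

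**Assumed inputs.** Adversity A is standardised. The distress score has SD 1 and correlation r with A of 0.3 or 0.5. Exposure prevalence is about 30%. The odds of exposure rise by a factor OR of 1.0, 1.5, 2.0 or 3.0 per SD of A. The true effect is 0, −0.2 or −0.3 SD (negative is better).

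**Formula.** With exposure depending on A alone, the bias of the unadjusted coefficient is r × d. Here d is the difference in mean A between exposed and unexposed caregivers. It follows from the logistic model with intercept log(0.3/0.7), integrated over a standard normal A.

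| OR per SD | d | bias, r = 0.3 | bias, r = 0.5 | simulated estimate, true effect −0.3 |
|---|---|---|---|---|
| 1.0 | 0 | 0 | 0 | about −0.30 |
| 1.5 | 0.39 | +0.12 | +0.20 | −0.18 to −0.11 |
| 2.0 | 0.63 | +0.19 | +0.32 | −0.11 to +0.02 |
| 3.0 | 0.89 | +0.27 | +0.45 | −0.04 to +0.15 |

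Simulation (600 replicates per setting, n = 200 and 400) agrees. With no true effect, the unadjusted estimate was +0.11 to +0.20 at OR 1.5, +0.19 to +0.32 at OR 2.0 and +0.26 to +0.45 at OR 3.0.

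**False findings of harm.** With no true effect and OR 1.5 to 3.0, the unadjusted model gave a significantly worse result in 12–84% of replicates at n = 200 and 16–100% at n = 400.

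**Adjustment.** Adjusting for the baseline score alone left +0.04 to +0.16 SD of bias at OR 1.5 to 3.0. Adding baseline adversity brought the null estimate to about 0.00, with significant worsening in 1–4% of replicates. A true effect of −0.3 was then recovered at about −0.30 and was significant in 60–77% of replicates at n = 200 and 92–96% at n = 400.

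**Timing.** In that simulation all confounding was present at baseline, so adjustment alone removed it. When need also arises after baseline (a separate simulation with 400,000 records, exposure 29–32%, true effect −0.20), the same-wave model gave −0.08 to +0.25 even after adjustment for baseline score and adversity. Relating earlier exposure to the later score, with the same covariates, gave −0.17 to +0.02. That is closer to the truth but not unbiased.

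**The case against.** Three stronger readings are tempting, and the documents support none of them.

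- **That the analysis is known to be unadjusted.** The article gives it one sentence and never says so. A covariate list is something a condensed article may leave to a full plan that is not shown. What the article does fix is the same-wave pairing.
- **That helped caregivers will look worse.** This is a prediction that depends on how strongly exposure follows need. Under the Hub's open-entry approach (Study phase 1), a conversation about adversity is meant for every caregiver, so being asked may depend little on need. With no dependence there is no bias. At OR 1.5 a true benefit of 0.3 SD keeps its sign.
- **That confounding alone could refute the logic model.** The text claims only association, and the programme theory is also tested with interviews, process data and improvement cycles.

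Two further points stand. The six-month recall means that much of the exposure precedes the score, so the design is not purely cross-sectional, although the order of need, help and symptoms within that window is unknown. And a baseline child score will not always exist: Table 1 switches from the ASQ-SE2 to the SDQ at age two, and pregnant women are eligible.

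None of this answers the central difficulty for intervention and referral, which are tied to need by definition.

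**Conclusion.** The point holds in a limited form. The same-wave regression, followed as written, mixes need with response, and the mixing probably runs against the hypothesis. Under the assumed inputs, the bias is about +0.1 to +0.45 SD for odds ratios of 1.5 to 3 per SD of adversity, and zero when exposure is unrelated to need. A true benefit of 0.3 SD could appear as anything from −0.18 to +0.15 SD over that range. Masking is therefore plausible, and reversal needs strong dependence on need: at this effect size it was clear only at OR 3 with r = 0.5.

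The case is strongest for intervention and referral and weakest for being asked. The sizes are illustrative, because the article supplies none of the inputs except n. This is a worthwhile, inexpensive improvement to a supporting analysis and does not undermine the study.

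**What to change.** 1. Adjust each regression for the baseline value of the score, the baseline 15-type adversity report, site and child age.
2. Add a lagged model with the exposure reported at 6 months and the score at 12 months, adjusted for the same covariates. This respects the ordering in the logic model.
3. For child mental health, use age-standardised scores or restrict to children with the same instrument at both waves. State how children with no baseline score, such as those of pregnant participants, are handled.
4. Interpret the intervention and referral results as associations open to residual confounding by need.

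**Cost.** The adversity report and the caregiver baseline scores are already collected, so for caregiver outcomes this is a change of analysis wording. Caregivers or children missing a baseline score or a wave must be imputed or are lost, most noticeably for child mental health. The lagged model does not account for help received between 6 and 12 months. It reduces, but does not remove, confounding by need that arises after baseline.

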#### Health economics analysis

Costs of the Hubs will be identified, including practitioner training, administration for referrals, personnel to oversee clinical implementation and other relevant costs. Downstream costs of services and potential cost-offsets will be collected and analysed to obtain the cost per additional child/or caregiver attending the Hub. Quality of life will be measured using the carer-specific measure (EQ-HWB-S^72^). An analysis of the value of unmet need will be conducted by determining whether (i) the child and family’s needs were met, (ii) no needs or (iii) unmet needs using the Ages & Stages Questionnaire or Strengths and Difficulties Questionnaire (SDQ) to determine perceived need compared with the level of service use.

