**Methods and analysis:**

This multisite convergent mixed-methods study will run over three phases to (1) develop the initial Hub programme theory through formative research; (2) test and, then, (3) refine the Hub theory using empirical data. Phase 1 involves co-design of each Hub with caregivers, community members and practitioners. Phase 2 uses caregiver and Hub practitioner surveys at baseline, and 6 and 12 months after Hub implementation, and in-depth interviews at 12 months. Two stakeholder groups will be recruited: caregivers (n=100–200 per site) and Hub practitioners (n=20–30 per site). The intervention is a co-located Hub providing health, social, legal and community services with no comparator. The primary outcomes are caregiver-reported: (i) identification of, (ii) interventions received and/or (iii) referrals received for adversity from Hub practitioners. The study also assesses child, caregiver, practitioner and system outcomes including mental health, parenting, quality of life, care experience and service linkages. Primary and secondary outcomes will be assessed by examining change in proportions/means from baseline to 6 months, from 6 to 12 months and from baseline to 12 months. Service linkages will be analysed using social network analysis. Costs of Hub implementation and a health economics analysis of unmet need will be conducted. Thematic analysis will be employed to analyse qualitative data.

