**Secondary outcomes**					
*Child*					
Infant temperament	Increase in the proportion of caregivers who report their infant is easier/much easier than average; assessed through single caregiver-reported item on infant temperament; has a moderate correlation (*r*=0.51) with the Easy-Difficult Scale (EDS) of Australian version short form of Revised Infant Temperament Questionnaire^78^; completed for one child* aged 0–8 in each family 0 to <2 years.	X		X	
Child mental health	Decrease in the mean scores for caregiver-reported internalising or externalising symptoms for their child. Completed for one child* in each family. For children aged 0 to <2 years: Ages & Stages Questionnaire Social-Emotional Second Edition (ASQ-SE2).^79^† For children aged ≥2 to 8 years: Strengths & Difficulties Questionnaire.^80^	X		X	
Global health	Increase in the mean scores of caregiver-reported general child health; assessed through single item (GHQ-S1) from Child Health Questionnaire^81^; completed for one child* aged 0–8 in each family.	X		X	
*Caregiver*					
Uptake of referrals	Increase in the proportion of caregivers who report uptake of referrals to other services in the past 6 months.	X		X	
Mental health	Decrease in the mean scores of caregiver-reported psychological distress as assessed by Kessler Psychological Distress Scale 6 (K6); 6-item.^82^	X		X	
Global health	Increase in means scores of caregiver-reported general health; assessed through single item of the Short Form Health Survey (SF-12).^83^	X		X	
Parental warmth, parenting hostility and efficacy	Increase in mean scores of parental warmth and efficacy; decrease in mean scores on parenting hostility. Three self-report subscales drawn from the Longitudinal Study of Australian Children (LSAC), Australia’s first nationally representative longitudinal study of child development which will allow for national comparisons of the study data^84^; assessing parental warmth, parenting hostility and efficacy. Parental warmth (6-items), parenting hostility (5-items) and parenting efficacy (4-items).	X		X	
Quality of life	Increase in mean caregiver quality of life scores calculated from the EuroQol Health and Well-being Instrument Short Form (EQ-HWB-S).^72^	X		X	

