Caregiver experience	Caregiver reported acceptability and feasibility of the Hub; Increase in the proportion of caregivers who report their satisfaction with Hub care as measured by three items from the Australia Bureau of Statistics Patient Experiences in Australia Survey.^85^	X		X	
Personal well-being	Increase in mean scores of caregiver-reported personal well-being outcomes measured by the Personal Well-being Index; 7 items.^86^	X		X	
*Practitioner*					
Identification of adversity	Increase in the proportion of practitioners who report asking about adversity in the past 6 months.		X		X
Intervention for adversity	Increase in the proportion of practitioners who report spending extra time or providing an intervention for adversity in the past 6 months.		X		X
Referrals for adversity	Increase in the proportion of practitioners who report referring caregivers to an intersectoral service for adversity in the past 6 months.		X		X
Practitioner experience	Practitioner reported acceptability and feasibility of the Hub; Increase in the proportion of practitioners who report feeling confident and competent to detect and support families experiencing adversity.		X		X
*System level*					
Strength and structure of intersectoral service linkages	Increase in the number and strength of service linkages between Hub practitioners as assessed through social network analysis (SNA) indicators for network density, degree, centrality and betweenness, and map of linkages between Hub practitioners based on i) contact, (ii) referrals to, (iii) referrals from, and (iv) quality of the relationship.^68–71^		X		X
Health economics outcomes	Costs of implementation of the Hub models, caregiver-reported intersectoral service usage and value of unmet need.	X		X	

*Caregivers with more than one child will respond to questions pertaining to one child in their family based on the child they are most concerned about.

†The ASQ-SE is limited by its design as a screening tool that may not be a sensitive outcome measure. The measure is used in this study because it more directly measures mental health and well-being than the ASQ.

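### Unmet need is to be judged for the child and the family, but need is read only from a child questionnaire, so family-level needs can go uncounted

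*Protocol article*

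**What the plan says.** The Health economics analysis section sets up a three-way classification. It asks whether "the child and family’s needs were met", whether there were none, or whether they went unmet, and it decides this "using the Ages & Stages Questionnaire or Strengths and Difficulties Questionnaire (SDQ) to determine perceived need compared with the level of service use". It names no other measure of need.

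Table 1 lists the corresponding tools under child mental health. The ASQ-SE2 is used below two years of age and the SDQ from two to eight. The caregiver completes them for one child, the one causing most concern. A footnote says the ASQ-SE was chosen "because it more directly measures mental health and well-being than the ASQ".

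Information about the family is collected elsewhere. Under Caregivers, "caregivers will report the frequency of 15 adversity types in the baseline survey". The types include finances, housing, family violence, parent mental health, immigration and discrimination. Table 1 adds the caregiver K6 at baseline, 6 and 12 months and, in its health economics row, service use across sectors at the same times.

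The economic section also intends to analyse downstream costs and offsets "to obtain the cost per additional child/or caregiver attending the Hub". The Abstract describes the intervention as one "with no comparator".

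**The concern.** The scope of the classification and the data that feed it do not match. The output is labelled as the need of child and family, while the input is a symptom score for one child. The section headed The current study defines the Hub as a response to family adversity across health, social, legal and community sectors. The needs that fall outside the rule are therefore ones the Hub was built to address.

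The value of unmet need is a listed outcome in Table 1, and the Dissemination section says the findings are meant to support scale-up to other services. A funder reading a low figure for family unmet need could take it to mean that few families have unaddressed social or legal needs, when the rule had no means of recording them.

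**Working it through.** The article reports no number for unmet need and no formula, so there is no figure to reproduce. The check sets the stated rule against the data sources and runs family types through it.

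**Inputs**

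- Unit classified: child and family (Health economics analysis).
- Measure of need: Ages & Stages Questionnaire or SDQ (same section).
- What those tools cover: one child's internalising or externalising symptoms (Table 1).
- Family-level data not used by the rule: caregiver K6 at all three waves (Table 1), and 15 adversity types, stated for baseline (Caregivers).
- Service-use side: reported across sectors (Table 1, health economics row).
- Eligibility: includes pregnant women (Caregivers).

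**Family types under the rule as written**

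| Child score | Family-level need | Recorded as | Correct for child and family |
|---|---|---|---|
| Low | None | No needs | No needs |
| Low | Present, served | No needs | Met |
| Low | Present, not served | No needs | Unmet |
| High, not served | Any | Unmet | Unmet |
| None (pregnant, no child yet) | Any | Cannot be scored | Depends on family need |

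The third row is the main problem. It does not depend on the cut-off chosen: whatever the threshold, a family-level need is invisible when the child falls below it. Where the child scores high and is served, the result depends on how service use is matched to need. The article does not say how, so nothing here rests on that case.

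**Direction.** Among families with a low-scoring child, the rule can lose unmet family needs but cannot add any. The error therefore runs towards understatement.

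**Size.** Let F be the share of families with a family-level need, m the share of those whose child scores low, and u the share of that group not receiving a relevant service.

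- Wrongly recorded as no needs: F × m.
- Of these, should be unmet: F × m × u.
- Of these, should be met: F × m × (1 − u).

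The documents give no value for F, m or u, so none of the three can be evaluated.

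**The two smaller points**

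- *Instrument name.* The economic section names the Ages & Stages Questionnaire, while Table 1 collects the ASQ-SE2. The Table 1 footnote treats the ASQ as a different tool. The SDQ agrees in both places.
- *Additional attendee.* If N people attend, N0 of them would have attended anyway and cost is C, the quantity is C ÷ (N − N0). The article does not say how N0 would be obtained. Its before–after contrasts, under Quantitative data analysis, are given for the primary and secondary outcomes. The quantity is undefined as it stands.

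**The case against.** **A child tool is a defensible choice.** The Introduction stresses the lack of Hub research focused on child mental health, and the child measures are scheduled at every wave. An article also leaves costing detail to a fuller plan. This stands for cut-offs and for the matching of services to need. It does not remove the mismatch, because both the family scope and the child-only measure are stated in the text.

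**Reported adversity is not service need.** The list records how often adversities occur, not whether a service is wanted or lacking. Counting any single item out of 15 could class most families as in need. This stands, and it is why a frequency threshold is required. It limits how family need can be defined, but does not make a child's score a measure of it.

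**The ASQ wording is probably shorthand.** The phrase is the opening of the ASQ-SE2's full title and is paired with the SDQ, as in Table 1. This stands. A reader might infer that an uncollected instrument will be used, but the text supports only a naming correction.

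**A stronger reading.** A reader might infer that both economic quantities will be wrong, or put a multiple on the cost error. The documents do not support that. Child need can still be classified. No denominator is stated for the cost figure, so a multiple would presuppose division by all attendees, which appears nowhere. A before–after attendance count remains possible, since the routine data under Process evaluation and quality improvement cycles are given only as examples. A percentage of mislabelled families would likewise rest on prevalences from outside the documents.

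**Conclusion.** The concern holds for the unmet-need classification. As stated, the rule records a family with a housing, violence or caregiver mental-health need and a low-scoring child as having no needs, so family unmet need is liable to be understated. The direction follows from the rule. The amount depends on three rates that the documents do not give.

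The conclusion assumes that the economic section means what it says, namely that the two child tools alone determine need. If a fuller plan already adds family measures, the article's sentence still needs correcting. The instrument name and the meaning of 'additional' are minor clarifications. All of this concerns a secondary economic output, and the primary outcomes are untouched.

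**What to change.** Report two classifications instead of one.

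- **Child need:** ASQ-SE2 or SDQ above a stated cut-off, compared with relevant service use, at each wave.
- **Family need:** caregiver K6 above a stated cut-off at each wave and, at baseline, reported adversity above a frequency threshold fixed in advance. Match each to the service use relevant to it.
- **Follow-up:** use the adversity list at 6 and 12 months only if it is repeated there. Otherwise state that family need at those waves rests on the K6 alone.
- **Fallback:** if none of this is done, relabel the output as unmet child mental-health need.

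In the same edit, align the Ages & Stages name with the ASQ-SE2 in Table 1. Then either report average cost per person served, or state the before–after attendance reference that 'additional' means and label it as uncontrolled.

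**Cost.** At baseline this is mainly analysis wording, since the K6, the adversity list and service use are already collected. Repeating the list would add items to the follow-up surveys. A broader definition will raise the share of families classed as in need, and the report should say that reported adversity is not the same as wanting a service.
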